## Abstract

**Background:**

Definitive concurrent chemoradiotherapy (dCCRT) is the gold standard for the treatment of locally advanced esophageal squamous cell carcinoma (ESCC). However, the potential benefits of consolidation chemotherapy after dCCRT in patients with esophageal cancer remain debatable. Prospective randomized controlled trials comparing the outcomes of dCCRT with or without consolidation chemotherapy in patients with ESCC are lacking. In this study, we aim to generate evidence regarding consolidation chemotherapy efficacy in patients with locally advanced, inoperable ESCC.

**Methods:**

This is a multicenter, prospective, open-label, phase-III randomized controlled trial comparing non-inferiority of dCCRT alone to consolidation chemotherapy following dCCRT. In total, 600 patients will be enrolled and randomly assigned in a 1:1 ratio to receive either consolidation chemotherapy after dCCRT (Arm A) or dCCRT alone (Arm B). Overall survival will be the primary endpoint, whereas progression-free survival, locoregional progression-free survival, distant metastasis-free survival, and treatment-related toxicity will be the secondary endpoints.

**Discussion:**

This study aid in further understanding the effects of consolidation chemotherapy after dCCRT in patients with locally advanced, inoperable ESCC.

**Trial registration:**

ChiCTR1800017646.

**Supplementary Information:**

The online version contains supplementary material available at 10.1186/s12885-024-12002-5.

## Background

Esophageal cancer is the eighth most prevalent cancer and the sixth leading cause of cancer-related deaths globally [1]. In China, among all cancers, esophageal cancer has the highest morbidity and mortality rates, respectively [2]. More than 90% of patients with esophageal cancer in China demonstrate squamous cell carcinoma accounts; in contrast, esophageal adenocarcinoma is frequently observed in Western countries [3]. For nearly two decades, definitive concurrent chemoradiotherapy (dCCRT) has been the gold-standard treatment for locally advanced, inoperable ESCC [4].

The RTOG 85-01 trial established the standard pattern of dCCRT for esophageal cancer [5]. In this trial, dCCRT group patients received radiotherapy in combination with two cycles of concurrent chemoradiotherapy (CCRT; cisplatin and 5-fluorouracil), followed by two cycles of consolidation chemotherapy (cisplatin and 5-fluorouracil). These results confirmed the efficacy of dCCRT in treating locally advanced esophageal carcinoma [5]. When using combined chemoradiotherapy, subsequent studies have widely adopted the treatment regimen of two cycles of CCRT followed by another two cycles of consolidation chemotherapy. Despite significant advancements in combined treatment modalities, locoregional recurrence remains the prevailing pattern of post-dCCRT recurrence in patients with esophageal cancer, with 2-year local recurrence rates ranging from 43% to 58% [4, 6–9]. The rationale for consolidation chemotherapy in dCCRT is also based on the hypothesis that the earlier the non–cross-resistant agents are used, the higher is the likelihood of increased cancer cell death [10]. Nevertheless, the efficacy of consolidation chemotherapy after dCCRT in ESCC management has not been assessed through randomized trials. Only a few retrospective studies have compared the effectiveness of dCCRT with or without subsequent consolidation chemotherapy [11–13]. Chen et al. reported that the consolidation chemotherapy following dCCRT did not yield significant progression-free survival (PFS; 25.4 vs. 23.0 months, *P* = 0.49) and OS (35 vs. 34.6 months, *P* = 0.9) improvements in patients with ESCC [11]. However, Adenis et al. asserted that patients who receive consolidation chemotherapy after dCCRT tend to have improved median overall survival (OS; 20.1 vs. 9.9 months) and 3-year OS rate (26.4% vs. 15.5%) [13]. Nonetheless, the bias and the sample size variance in these retrospective studies have led to this issue remaining debatable. Furthermore, Wu et al. also showed that patients with ESCC did not benefit from the consolidation chemotherapy after dCCRT on both PFS and OS [12]. In the context of relevant data scarcity, a prospective non-inferiority randomized trial investigating the impact of consolidation chemotherapy after dCCRT in patients with ESCC is urgently needed.

## Rationale

To the best of our knowledge, the use of consolidation chemotherapy following dCCRT for locally advanced, inoperable ESCC was first reported over two decades previously. Furthermore, despite advancements in intensity-modulated radiotherapy technology (IMRT), dependable evidence substantiating the efficacy of consolidation chemotherapy is lacking. According to the limited evidence reported thus far, compared with dCCRT alone, consolidation chemotherapy after dCCRT does not provide a significant survival benefit in patients with locally advanced, inoperable ESCC. As such, this will be the first multicenter, prospective, phase III randomized controlled trial to provide strong evidence regarding the efficacy of consolidation chemotherapy following dCCRT in patients with inoperable ESCC.

## Methods

### Study design

This will be a prospective, two-arm, phase III randomized controlled trial aimed at assessing non-inferiority of dCCRT alone to consolidation chemotherapy following dCCRT in patients with locally advanced, inoperable ESCC. Each patient will be randomly assigned at a 1:1 ratio to receive either consolidation chemotherapy after dCCRT (Arm A) or dCCRT alone (Arm B; Fig. 1).

**Fig. 1 Fig1:**
[figure not shown]
Trial diagram

Randomization was stratified by tumor location (cervical *V* thoracic) and tumor stage (II *V* III *V* IV). Written informed consent will be obtained from all patients before participation in this trial. All participating medical centers are well-experienced in radiotherapy and chemotherapy delivery.

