### Sample size considerations

The sample size is based on data from a retrospective study [11] and a phase III randomized controlled trial [14]—which suggested that dCCRT yields 2-year OS rates of ≥60% and 56%, respectively. Therefore, we hypothesized that consolidation chemotherapy after dCCRT (Arm A) and dCCRT alone (Arm B) will yield 2-year OS rates of approximately 60% and 48%–65%, respectively. According to Power Analysis and Sample Size (version 15.0), these rates will be obtained with a two-sided type I error of 5% with 90% power, a type II error (β) of 20% with 15% noninferiority margin, and a dropout rate related to dCCRT or loss to follow-up of 5%. Therefore, the final sample size will be 600, with a 1:1 allocation in each arm.

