### Statistical analysis

Data analyses will be performed according to the intention-to-treat principle in all randomized patients. Between-group comparisons will be performed using chi-squared and Fisher’s exact test for categorical parameters and Student’s *t* test for normally distributed continuous variables or the Mann–Whitney *U* test or analysis of variance for nonnormally distributed continuous variables. Survival rates will be calculated using the Kaplan-Meier method, and comparisons between the groups will be performed using the log-rank test. The difference will be considered statistically significant at a *P* value of <0.05.

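### Randomisation is stratified by tumour location and stage, but the stated log-rank comparison does not mention the strata: a minor mismatch, free to correct

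*Protocol article*

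**What the plan says.** Under Study design, after the Fig. 1 caption, the article states: "Randomization was stratified by tumor location" (cervical or thoracic) and by tumour stage (II, III or IV). That makes 2 × 3 = 6 cells.

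The Statistical analysis section names specific methods. For time-to-event outcomes it says "Survival rates will be calculated using the Kaplan-Meier method" and "comparisons between the groups will be performed using the log-rank test", and then gives the decision rule "The difference will be considered statistically significant at a *P* value of <0.05". It mentions neither stratification nor covariate adjustment.

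Two further statements bear on the consequences. The Study design section gives the aim as "assessing non-inferiority of dCCRT alone to consolidation chemotherapy following dCCRT". Sample size considerations expects that Arms A and B "will yield 2-year OS rates of approximately 60% and 48%–65%, respectively", and sets a margin of 15% beside those rates. No margin on the hazard-ratio scale appears anywhere.

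**The concern.** Stratified randomisation balances the arms on location and stage, which removes part of the chance variation between them. An analysis that ignores the strata still counts that variation in its standard error, so the test is somewhat conservative and precision bought by the design goes unused.

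A Cox hazard ratio is also non-collapsible. When prognostic factors are left out, it moves toward 1 relative to the within-stratum value, even with perfect balance.

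The same sentence of the plan governs OS, PFS, LPFS and DMFS, so all four are affected. If the article does not say whether the strata enter the analysis, stratified and unstratified results also remain open to choice after the data are seen.

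**Working it through.** **The plan's own figure.** The article gives no number for this point. Its one computed figure, N = 600, does not depend on stratification and is taken as given below. It does not reproduce as a non-inferiority size. With 60% in both arms, a 15% margin, two-sided 5% and 90% power, n per arm = (1.960 + 1.282)² × 2 × 0.60 × 0.40 / 0.15² = 224.2, rounded up to 225. The total is 450, and 450/0.95 gives 474. At 80% power the totals are 336 and 354. That is a separate matter.

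**Inputs from the article.** Six strata, 1:1 allocation, 600 patients, Arm A 2-year OS 60%, margin 15%, and follow-up of at least 3 years.

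**Assumptions, not in the article.** Stage shares 20/50/30%; 15% cervical; permuted blocks of 4; exponential survival; follow-up 36 to 60 months with light censoring. Prognostic hazard ratios per stage step and for location: weak 1.3 and 1.0, moderate 1.5 and 1.25, strong 2.0 and 1.5. There were 12,000 simulated trials per scenario.

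**Margin on each scale.** At the margin, Arm B 2-year OS is 60% − 15% = 45%. The overall hazard ratio implied by those rates is ln(0.45)/ln(0.60) = 1.563. The within-stratum hazard ratio that produces the same overall rates is larger: 1.571, 1.583 and 1.623 for weak, moderate and strong strata.

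**Results.** Attenuation is 1 − (unstratified HR / stratified HR).

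| | Weak | Moderate | Strong |
|---|---|---|---|
| Equal arms: log-rank rejection, unstratified (nominal 5%) | 4.7% | 4.6% | 3.5% |
| Equal arms: log-rank rejection, stratified | 5.0% | 5.3% | 4.7% |
| At margin: mean HR, unstratified | 1.562 | 1.553 | 1.542 |
| At margin: mean HR, stratified | 1.574 | 1.582 | 1.625 |
| Attenuation | 0.8% | 1.8% | 5.1% |
| At margin: mean 2-year Kaplan-Meier difference, unstratified | −0.151 | −0.150 | −0.150 |
| False NI (nominal 2.5%): unstratified Kaplan-Meier against 15% | 2.1% | 2.2% | 1.8% |
| False NI: unstratified HR against 1.563 | 2.2% | 2.7% | 2.3% |
| False NI: unstratified HR against within-stratum margin | 2.5% | 3.6% | 5.8% |
| False NI: stratified HR against within-stratum margin | 2.2% | 2.7% | 2.4% |

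**Simulation error.** At 2.5% it is √(0.025 × 0.975/12,000) = 0.14 points; at 5% it is √(0.05 × 0.95/12,000) = 0.20 points. The loss of rejection rate under equal arms is therefore clear with strong strata (3.5%). With weak or moderate strata it lies within two simulation errors of 5%.

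**Why the scales differ.** The overall 2-year survival difference is an average of stratum differences, so omitting balanced strata does not shift it. Only its standard error is overstated: with strong strata the mean estimated standard error was 0.0408 against an empirical 0.0387, or 0.0408/0.0387 − 1 = 5%. The hazard ratio has no such averaging property.

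**The case against.** **The defect is read from silence.** The Statistical analysis section never calls the test unstratified. It is a short paragraph in a condensed article, and an analysis plan that is not shown may specify stratification. This stands as a reason for low severity and moderate confidence. It does not remove the point: the section lists its tests by name, and a stratified log-rank test is a different test from the one named.

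**A stronger reading is tempting.** Attenuation toward no difference favours the hypothesis under test in a non-inferiority trial, so a reader might infer that the plain log-rank analysis raises the risk of a false non-inferiority claim. The article does not support this. Its only margin stands beside 2-year OS rates and reads as an absolute difference. On that scale the estimate is not attenuated and the error is at or below nominal. An unstratified hazard ratio set against 1.563, its equivalent on the overall scale, is also close to nominal. Excess error appears only if a within-stratum margin is paired with an unstratified hazard ratio. Treating 1.563 as a within-stratum value would create the excess artificially, because 1.563 is derived from overall rates.

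**Stratifying misses the larger gap.** This also stands. A log-rank P value contains no margin, so it cannot show non-inferiority, stratified or not. The section never compares a confidence limit with the 15%, and stratifying alone would not cure that.

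**Conclusion.** The point holds as a minor mismatch between design and analysis. Across the assumed range of prognostic strength, ignoring the strata makes the log-rank test slightly conservative under equal arms (3.5% to 4.7% at nominal 5%) and brings the hazard ratio about 1% to 5% closer to 1 than the stratified estimate. There is no demonstrated increase in false non-inferiority on the absolute 2-year OS scale (1.8% to 2.2% against 2.5%). Inflation to 3.6% or 5.8% would need a within-stratum hazard-ratio margin, which the article does not state, and moderately or strongly prognostic strata.

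The sizes rest on assumed stage and location effects, stratum shares, block size and accrual pattern. That the planned test is unstratified is itself inferred from an article that does not say either way.

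**What to change.** In the Statistical analysis section, specify:

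- a log-rank test and a Cox model stratified by tumour location and stage, for OS, PFS, LPFS and DMFS;
- a 2-year Kaplan-Meier OS difference, weighted by the overall stratum shares, for the non-inferiority confidence interval, so that it targets the overall difference to which the 15% appears to refer;
- a pre-specified rule for pooling sparse cells, for example collapsing location within stage. Under the shares assumed above, cervical stage II would hold 0.15 × 0.20 × 600 = 18 patients, about 9 per arm.

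State the scale of the 15% margin in the same place. If a hazard-ratio margin were ever used, it and the estimate must both be overall or both within-stratum. With strong strata, a stratified hazard ratio set against the overall value 1.563 gave 1.0% false non-inferiority, well below 2.5%.

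The cost is a few lines of text. The factors are already recorded for randomisation and N stays at 600. The article reports 200 patients recruited with recruitment continuing, so the change can be fixed before any analysis. The performance of the stratum-weighted difference was not simulated here.

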### Target population

Male and female patients with histologically proven ESCC who provide their written informed consent are eligible for this trial. The principal investigator will thoroughly evaluate and confirm that patients fulfill all the inclusion criteria.

### Sample size considerations

The sample size is based on data from a retrospective study [11] and a phase III randomized controlled trial [14]—which suggested that dCCRT yields 2-year OS rates of ≥60% and 56%, respectively. Therefore, we hypothesized that consolidation chemotherapy after dCCRT (Arm A) and dCCRT alone (Arm B) will yield 2-year OS rates of approximately 60% and 48%–65%, respectively. According to Power Analysis and Sample Size (version 15.0), these rates will be obtained with a two-sided type I error of 5% with 90% power, a type II error (β) of 20% with 15% noninferiority margin, and a dropout rate related to dCCRT or loss to follow-up of 5%. Therefore, the final sample size will be 600, with a 1:1 allocation in each arm.

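### The sample-size paragraph states both 90% power and a 20% type II error and gives Arm B a range instead of one planning rate, so 600 cannot be verified and at most one stated power can be right.

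*Protocol article*

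**What the plan says.** The protocol article describes a non-inferiority trial of dCCRT alone (Arm B) against dCCRT followed by consolidation chemotherapy (Arm A), with overall survival as the primary endpoint. The inputs are all in the section Sample size considerations:

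- **Source rates:** two earlier studies, a retrospective one and a randomised one, are cited as showing that "dCCRT yields 2-year OS rates of ≥60% and 56%, respectively".
- **Planning rates:** Arms A and B "will yield 2-year OS rates of approximately 60% and 48%–65%, respectively".
- **Error rates and margin:** "two-sided type I error of 5% with 90% power, a type II error (β) of 20% with 15% noninferiority margin".
- **Attrition:** "a dropout rate related to dCCRT or loss to follow-up of 5" per cent.
- **Result:** "the final sample size will be 600, with a 1:1 allocation in each arm".

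The abstract repeats the total: "In total, 600 patients will be enrolled and randomly assigned in a 1:1 ratio". The section Assessments during the treatment phase places randomisation after dCCRT, for patients who have not progressed. The Statistical analysis section takes all randomised patients as the analysis set.

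**The concern.** The sentence on error rates contains a contradiction that no other section resolves. A β of 20% is 80% power, and 90% power is a β of 10%.

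Arm B is the arm whose non-inferiority is to be shown, yet it has a 17-point range in place of a planning rate. The power of a non-inferiority comparison depends steeply on how far the tested arm's true rate lies from the margin. The lower end of the range is 12 points below Arm A, only 3 points inside a 15-point margin. The upper end is 5 points above Arm A. No single power figure can hold across that span.

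At stake is the reading of the final result. If the trial fails to show non-inferiority, readers will ask whether it had adequate power, and the protocol gives them two answers and no assumption to attach either to.

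A smaller point concerns the 5% allowance, which is worded to include dropout related to dCCRT. Because randomisation follows dCCRT, at least part of that dropout would occur before a patient can count among the randomised.

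**Working it through.** **Inputs from the protocol article:** Arm A 60%; Arm B 48%–65%; margin 15%; two-sided alpha 5%; power 90% or 80%; attrition 5%; total 600 at 1:1, so 300 per arm and 300 × 0.95 = 285 evaluable per arm.

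**Assumptions the article does not settle:** the margin is absolute (15 percentage points in 2-year survival), and two-sided 5% means one-sided 2.5% for non-inferiority.

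**The plan's own figure.** It cannot be reproduced as a single calculation, because the text fixes neither one power nor one Arm B rate. The check therefore runs in two directions.

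**Step 1: the N that each named rate requires.** With pA = 0.60 and pB the Arm B rate,

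n per arm = (z_α + z_β)² × [pA(1 − pA) + pB(1 − pB)] / [0.15 − (pA − pB)]²

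Here (1.960 + 0.842)² = 7.849 for 80% power and (1.960 + 1.282)² = 10.507 for 90%. Each arm is rounded up, divided by 0.95 and rounded up again.

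Example, pB = 0.60: 7.849 × 0.48 / 0.15² = 167.4, so 168; 168/0.95 gives 177 per arm, total 354. For 90% power: 10.507 × 0.48 / 0.0225 = 224.2, so 225; 225/0.95 gives 237 per arm, total 474.

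Example, pB = 0.56: the variance sum is 0.24 + 0.2464 = 0.4864 and the distance to the margin is 0.11. Then 7.849 × 0.4864 / 0.0121 = 315.5, so 316, and the total is 666.

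| Arm B rate | Where it comes from | Total N, 80% power | Total N, 90% power |
|---|---|---|---|
| 48% | lower end of range | 8,990 | 12,036 |
| 56% | cited randomised trial | 666 | 892 |
| 60% | equal to Arm A; cited retrospective study (≥60%) | 354 | 474 |
| 65% | upper end of range | 194 | 260 |

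None of these is 600.

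**Step 2: the power that 600 delivers.** With 285 per arm,

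power = Φ( [0.15 − (0.60 − pB)] / SE − 1.960 ), SE = √{[0.24 + pB(1 − pB)] / 285}

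Example, pB = 0.56: SE = √(0.4864/285) = 0.0413; 0.11/0.0413 = 2.663; Φ(0.703) = 0.759.

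| True Arm B rate | Power with 600 |
|---|---|
| 48% | 10.8% |
| 56% | 75.9% |
| 56.6% | 80% |
| 58.3% | 90% |
| 60% | 95.5% |
| 65% | 99.9% |

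The 56.6% and 58.3% rows are solved backwards from 600. The midpoint of the stated range, (48% + 65%)/2 = 56.5%, gives 610 for 80% power.

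**Step 3: does the scale matter?** Suppose the margin is converted to a hazard ratio, ln 0.45 / ln 0.60 = 1.563, with a log-rank calculation using 2-year deaths only and 5% attrition. The totals for 80%/90% power are then 416/556 at an Arm B rate of 60%, 770/1,031 at 56%, 233/312 at 65% and 10,117/13,543 at 48%. Again none is 600, and the spread is as wide.

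**The case against.** The strongest reply is that 600 has not been shown to be wrong, and that is correct. A reader might compare 600 with the 354 or 474 needed when both arms are at 60% and conclude that the plan's inputs do not produce its total. The article never fixes Arm B at 60%. At the cited trial's 56% the requirement is 666 or 892, so even the direction of any discrepancy depends on a rate that the reader supplies. With the stated margin, alpha and attrition, Arm B rates inside the stated range do lead to about 600. They are inferred or solved backwards, so they show that 600 is compatible with the inputs, not that they were used.

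A reader might also infer that the stated power is wrong outright. Two powers are stated, so at least one is wrong, but the text does not say which. If both arms are truly at 60%, 600 patients exceed both figures.

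Other designs can be found that reach about 600, such as a 12-point margin with a one-sided 5% test, or a superiority comparison of 60% with 48%. Nothing in the article says that either was used, and it describes non-inferiority throughout. Alpha and the margin are each stated once and without contradiction; only the margin's scale is left open.

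On what 600 counts, the abstract and the 1:1 wording both point to randomised patients, so only the attrition phrase is loose.

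What the reply does not touch is the contradiction between 90% power and a 20% β, and the absence of one Arm B planning rate.

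**Conclusion.** The point holds in a limited form. The article gives two incompatible powers for one calculation and no single Arm B rate. At most one of the powers can be right, and 600 cannot be verified. Across the stated Arm B range the power of 600 patients runs from about 11% to 99.9%; at the cited randomised trial's 56% it is about 76%, below both stated figures. The total matches none of the rates that the section names but is compatible with others inside the range, so the finding is that 600 is unverifiable, not that it is mistaken.

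The contradiction and the missing rate are plain from the text and rest on no assumption. The power figures rest on an absolute 15-point margin at 2 years, one-sided 2.5%, Arm A at 60% and 285 evaluable patients per arm. The attrition wording is a minor, related ambiguity.

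**What to change.** Keep the total of 600, the 15% margin and the two-sided 5% alpha, and rewrite the section as follows:

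1. State the margin's scale (absolute, at 2 years, if that is what is meant).
2. State one Arm B planning rate, preferably the one entered in the software. Recruitment is under way, so if that record cannot be recovered, say so and choose the rate without reference to outcomes by arm.
3. Delete whichever of the 90% power and the 20% β is not meant, and give the power that 600 delivers at the chosen rate: for example 95.5% at 60%, or 76% at 56%. Show the calculation.
4. Move 48%–65% out of the hypothesis and into a table of power against the true Arm B rate, such as the one in the working.
5. Say that 600 counts randomised patients and that the 5% applies to loss after randomisation, since randomisation follows dCCRT.

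The cost is rewording and one recalculated figure. The sponsor may have to report a lower power than either of those now stated, if the chosen rate is below about 56.6%. No extra enrolment is proposed.
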